### Procedures

Identical processes for data collection will operate at the three sites. The clinical assessment incorporates a combination of clinician, consumer, clinician-and-consumer and carer/family completed measures (see Table 2). For the purposes of this study a Carer is considered to be a person (e.g. family member or friend) who the Consumer nominates as having a significant unpaid caring role for them. Staff for which each measure reflects their core-skills set and routine practice will be responsible for measure completion (see Table 3).

The research protocol was explained to staff prior to the commencement of data collection. Each discipline completing relevant assessments will work to maximise fidelity through regular peer based supervision. Standardised training in the use of routine outcome measures is provided to all staff, this includes opportunities to calibrate scoring of HoNOS and Life Skills Profile-16 (LSP) [48] across the study sites. Fidelity of data relating to symptom measures will be enhanced through the use of the anchored scoring version of the Brief Psychiatric Rating Scale (BPRS-A) [62] and a semi-structured interview guide developed in an Australian context for raters with low-clinical experience [63], as well as a structured interview guide for the Scale for the Assessment of Negative Symptoms (SANS) measure [64]. Inter-rater reliability data will also be calculated from calibration sessions for the BPRS and SANS involving relevant staff.

A research assistant will collate the data from the pre-admission and post-discharge phases from established administrative data sets, where the relevant information is routinely collected.

As is commonly expected in health research [65, 66], it is anticipated that missing data will be present in both the administrative datasets and assessment battery. Categorical codes will be available for non-completed consumer and carer measures, and for clinician rated measures dependent on structured assessment. These codes will designate the reason for non-completion as being due to refusal by the consumer/carer or due to the measure not being offered to the consumer/carer. Missing Values Analysis will be completed in SPSS Version 22 and it is planned for missing data to be handled using the multiple imputation method [67] assuming this is missing at random. Characteristics and patterns of missing data, and the assumed mechanisms will be reported.

### Analysis

The quantitative analysis will be undertaken in SPSS Version 22 and statistical significance will be assessed at a level of 0.05:The cohort of consumers utilising the services across the three sites will be defined using descriptive statistics. Differences between the sites and staffing models will be examined using t-tests and chi-squared analyses. Assuming comparability of the cohorts is established it is planned that the data from the two integrated staffing model sites will be able to be combined.In order to answer the question of equivalence of the integrated and clinical staffing model for CCUs, differences in the total HoNOS score pre admission and post discharge will be assessed using a t-test or Mann–Whitney U test depending on the normality of the distribution.The question of whether CCU rehabilitation care results in change in specific clinically relevant outcome domains, will be answered through analysis of the secondary outcome measures. It is anticipated that data from the secondary outcome measures will be dichotomised and subjected to Mann–Whitney U analysis with appropriate correction for multiple comparisons.Predictors of change in psychosocial functioning following CCU care will be explored using hierarchical linear regression modelling. The dependent variable is the same as the primary outcome variable for the overall study, mean change in total HoNOS score pre admission and post discharge from CCU care. The independent variables will be entered cumulatively with the organisational (Level 3) variable considered first, followed by the site related (Level 2) variables and then the consumer (Level 1) variables. A hierarchical approach is appropriate given the expectation of inter-correlation between the predictors [68].

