### Quantitative methodology

#### Design

A longitudinal, prospective cohort design is used to examine outcomes of consumers under the clinical and integrated staffing models. The methodology has been developed with consideration of the STROBE Statement [33] and it is intended that results will be reported in a manner consistent with these guidelines. Principles of relevance to the quality reporting of equivalence studies have also been considered [34]. Prospective data will be obtained from a clinical assessment battery at three time points: admission, discharge and the 0–12 months post-discharge (see Table 2). Supplementary data will also be available retrospectively for the period 0–12 months prior to CCU admission from routine administrative data sets.

**Table 2 Tab2:** Routine clinical assessment battery and administrative data collection over the baseline, admission, discharge and follow-up collection points

Domain		Measure	Baseline (−12–0 months)	Admission (0–6 weeks post)	Discharge (0–6 weeks prior)	Follow-up (0–12 months)
Administrative data		Health of the Nation Outcome Scale (HoNOS) [26]^A^	X	X	X	X^1^
		Life Skills Profile (LSP-16) [48]^B^	X^*^	X	X	X^2^
		Mental Health Inventory (MHI-38) [51]^B^	X	X	X	X^2^
		Mental health related Emergency Department presentations	X	X	X	X^2^
		Psychiatric inpatient bed days	X^*^	X	X	X^2^
Clinical assessment battery	Symptom measures	Alcohol Use Disorders Identification Test (AUDIT) [60]		X^*^	X	
		Brief Psychiatric Rating Scale (BPRS) [46]		X	X^2^	
		Scale for the Assessment of Negative Symptoms (SANS) [87]		X	X^2^	
	Functional Cognition	Allen’s Cognitive Levels (ACL) [59]		X^*^	X	
	Social-function	Social Functioning Scale (SFS) [88]		X^*^	X^2^	
	Functional	Perceive Recall Plan & Perform System of Task Analysis (PRPP) [89]		X	X	
	Recovery	Stages of Recovery Instrument (STORI-30) [49]		X^*^	X^2^	
	Carer burden	Burden Assessment Scale (BAS) [90]		X	X	
		Adult Carer Quality of Life (AC-QoL) [50]		X	X^2^	

^A^ HoNOS is routinely collected on admission and discharge from inpatient, community residential and ambulatory services, and 3-monthly review periods in the non-inpatient settings

^B^ LSP-16 and MHI are routinely collected on admission, discharge and 3-monthly review in community residential and ambulatory services

^1^ Primary outcome measure, examining change in total score between the Baseline and Follow-up periods

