### Measures

#### Primary outcome measure

The primary outcome measure will be change in psychosocial functioning as measured by total score on the HoNOS [37]. It is hypothesised that there will be no significant difference in the mean change in highest total HoNOS score recorded in the 0–12 months prior to CCU commencement and the highest score recorded 0–12 months post CCU discharge for consumers under the clinical and integrated staffing model. The total HoNOS score has been selected as the primary outcome measure as it:Has high validity, reliability and sensitivity to change, as well as routinely informing service policy and planning decisions in Australia [38];Is considered appropriate for tracking changes in social functioning over time, and more sensitive in doing so than the CANSAS (a needs based measure) [39];Has an embedded role in individual outcome assessment in Australia and New Zealand [38, 40, 41] and there is evidence that it is being regularly utilised in care planning [42, 43]Is supported by an established national assessment protocol and training processes to facilitate inter-rater reliability [38], and with evidence to support higher levels of acceptability [44] and completion than the other core measures of routine outcome suite [38]It is used and available across multiple international settings [45], increasing the replicability of the methodology.

Utilising the criterion of the highest (i.e. greatest dysfunction) score in the 12-month period pre and post CCU entry limits the risk of conflating the benefits of active rehabilitation support with the benefits associated with support and accommodation in the CCU setting.

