There are inherent limitations with relying on routinely collected administrative and clinical data, including missing data and recording bias [36]. Furthermore, the absence of blinding of raters provides a potential source of bias, however the primary outcome assessments in during the baseline and discharge periods will be completed by trained assessors independent of the CCU context. The absence of randomized allocation between the staffing models hinders our ability to make causal inferences regarding relationships between service provision and changes in outcome over time. However, the inappropriateness of running randomized placebo-controlled trials in socially complex services with reference to ethical and practical barriers has been acknowledged in the literature [30]. Regardless, the utility of equivalence testing depends in part on the underlying assumption that the comparator has been convincingly proven to have superior efficacy to placebo [77]. This assumption cannot be definitively asserted on the basis of the available literature.

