The naturalistic approach to sample selection confers both benefits and costs. Whilst the defined exclusion criterion aims to facilitate inclusion of only participants initially deemed to align with the model of service, this inclusive approach risks masking the effectiveness and differences between the two treatment arms through the inclusion of participants who do not complete their planned rehabilitation. Whilst the option of a per-protocol analysis approach [34], including only those participants whose CCU discharge was planned, will be available such an approach would not reflect the reality of rehabilitation practice. It has been argued that limited benefits are to be expected through provision of rehabilitation care without consumer engagement in the process [78]. There is an emerging interest in engagement scales for use in residential rehabilitation settings, including adaptation of an established measure used in assertive community treatment [16]. However, the broad suitability of this measure in application has not yet been established. Engagement with rehabilitation support over the CCU stay is not being specifically measured in this study. It is anticipated that the qualitative interviews with consumers will provide rich detail about relative levels of engagement under the two staffing models. Length of stay (whether a consumer remains for the minimum 6-month length of stay detailed in the model of service) will provide an additional proxy measure of engagement.

The longitudinal approach to sampling adds additional complexity to the evaluation. There is an expectation that service delivery will change over time. Generalizability of findings may also be affected by the expectation of incomplete sampling and site related differences in referral patterns. Given this, careful consideration of the characteristics of participants and non-participants at each is site is warranted.

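### The primary comparison of non-randomised units uses no covariates, and no other planned analysis supplies a case-mix-adjusted staffing estimate

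*Protocol article*

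**What the plan says.** **Design and outcome.** Under Design: "A longitudinal, prospective cohort design is used to examine outcomes of consumers under the clinical and integrated staffing models". The Primary outcome measure section hypothesises "no significant difference in the mean change in highest total HoNOS score recorded in the 0–12 months prior to CCU commencement" and the corresponding post-discharge score, between the two staffing models.

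**Primary test.** Under Analysis (quantitative), the pre-post HoNOS difference "will be assessed using a t-test or Mann–Whitney U test depending on the normality of the distribution", and "statistical significance will be assessed at a level of 0.05". No covariate is named.

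**Baseline comparison and pooling.** The same section states: "Differences between the sites and staffing models will be examined using t-tests and chi-squared analyses". The next sentence begins "Assuming comparability of the cohorts is established it is planned that the data from the two integrated staffing model sites" and says that they can then be combined.

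**Covariates available.** Table 2 lists HoNOS, LSP-16 and psychiatric inpatient bed days for the 12 months before admission. The section on secondary outcomes and descriptive data lists age, gender, education, diagnosis and other characteristics.

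**The regression.** Predictors of HoNOS change are explored by hierarchical linear regression. Staffing model enters first, then site and length of stay, then consumer variables (Table 4). Predictors are kept or dropped at the .05 level.

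**Acknowledged limits.** The Discussion says: "The absence of randomized allocation between the staffing models hinders our ability to make causal inferences". It also expects "site related differences in referral patterns".

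**The concern.** Consumers are not allocated to a staffing model; they receive the model that their unit operates. Table 1 shows that the referring districts differ in services. Only Bayside's has inpatient rehabilitation beds, only Coorparoo's has a transitional housing team, and Bayside's lacks both a non-residential rehabilitation team and a homelessness team. Such differences can affect who is admitted and how consumers score before and after the stay.

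With no covariates, a case-mix difference passes straight into the contrast. In an equivalence question this harms in both directions: it can produce a difference that staffing did not cause, or cancel a real one and be read as equivalence. The result is meant to inform staffing guidelines. A change score subtracts baseline HoNOS but does not adjust for it, and the baseline here is the worst score in a 12-month window, which is prone to regression to the mean.

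**Working it through.** The article gives no figure of its own on this point to reproduce. Its only input used here is the expected minimum sample of 60 integrated and 40 clinical consumers (Sample section). The 30/30 split between Bayside and Logan, the pre-post correlations and the imbalances are assumptions. Tests are taken as two-sided at 0.05.

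**1. What the baseline tests can detect.** Power ≈ Φ(d/√(1/n₁+1/n₂) − 1.96), with d the imbalance in SD.

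| Contrast | d | d/√(1/n₁+1/n₂) | Power, normal | Power, t-test |
|---|---|---|---|---|
| Bayside v Logan, 30 v 30 | 0.3 | 1.16 | 21% | 21% |
| Bayside v Logan, 30 v 30 | 0.5 | 1.94 | 49% | 48% |
| Integrated v clinical, 60 v 40 | 0.3 | 1.47 | 31% | 31% |
| Integrated v clinical, 60 v 40 | 0.5 | 2.45 | 69% | 68% |

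Splitting the 60 roughly by bed numbers (33 v 27) gives nearly the same: 21% and 47% by t-test. The first two rows bear on pooling; the last two bear on the primary contrast.

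**2. Chance findings.** Eight descriptors are fixed before or at admission: age, gender, ethnicity, marital status, education, diagnosis, treatment order status and medication. If tested as independent variables, the chance of at least one false difference in a contrast is 1 − 0.95⁸ = 34%.

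**3. Bias of the change score.** Let the groups differ by d SD in baseline HoNOS, with pre-post correlation ρ, no staffing effect, and both groups regressing to a common mean. The expected difference in change has size d(1 − ρ), and the group that starts worse appears to improve more. The SD of change is √(2(1 − ρ)).

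| ρ | Bias, d = 0.3 | Bias, d = 0.5 | False-positive rate, d = 0.3 | False-positive rate, d = 0.5 |
|---|---|---|---|---|
| 0.3 | 0.21 SD | 0.35 SD | 13% | 30–31% |
| 0.5 | 0.15 SD | 0.25 SD | 11% | 23% |
| 0.7 | 0.09 SD | 0.15 SD | 9% | 16% |

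Rates are from 20,000 simulated studies of 40 v 60 per setting and agree with the noncentral t distribution. A linear model with baseline HoNOS as covariate had bias near 0 and a rate near 5% throughout.

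As a yardstick, 60 v 40 detects (1.96 + 0.84) × √(1/40 + 1/60) = 0.57 SD with 80% power. A bias of 0.15–0.25 SD is 26–44% of that.

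**4. Does a non-significant baseline test protect?** At ρ = 0.5, among simulated studies in which the baseline HoNOS test between models was non-significant, bias was still 0.10 SD (d = 0.3) and 0.14 SD (d = 0.5).

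**5. Does the planned regression supply the adjusted estimate?** No, for four reasons:
- Table 4 does not include baseline HoNOS.
- It includes length of stay, mode of discharge and STORI-30 change, which arise after admission and may lie on the path from staffing to outcome.
- Covariates stay or go by p-value.
- Staffing model is a function of site. An intercept, a staffing indicator and indicators for Bayside and Logan make four columns of rank 3. Staffing enters first, so its coefficient has no consumer adjustment at that step; once site has entered, it cannot be estimated separately.

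**The case against.** **The change score already removes stable level differences, and the better model for pre-existing groups is disputed.** This stands in part. If a baseline difference is permanent, so that each group regresses to its own mean, the change score is unbiased and the baseline-adjusted model is off by d − ρd = d(1 − ρ), the same 0.15–0.25 SD at ρ = 0.5. The data cannot settle which holds. That supports reporting both and stating the assumption; it does not support a comparison free of all case-mix covariates.

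**The limits are disclosed.** The Discussion concedes non-random allocation, referral differences and site idiosyncrasies. Disclosure removes no measured confounding.

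**An unseen analysis plan may add adjustment.** It may. But this article does not leave the primary method open: it names a covariate-free test.

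**Stronger readings that the article does not support.**
- A reader might infer that the primary test is dropped if the baseline tests find differences. The condition governs only pooling of Bayside and Logan; the integrated-versus-clinical test follows with no condition. Nor does the article state that non-significance means comparable. That is inferred from two adjacent sentences.
- A reader might take the disadvantage ranks of 90, 83 and 46 in Table 1 as describing the referral populations. They are listed under Location and refer to the unit's local government area. The service differences are the district-level evidence.
- A reader might measure the bias against an equivalence margin. The article gives none.
- A reader might expect adjustment to isolate the staffing effect. With one clinical unit, site and district are completely aliased with staffing model.

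**Conclusion.** The concern holds in limited form. The article fixes an unadjusted comparison of non-randomised groups as its primary analysis, and its only covariate model cannot give a usable adjusted staffing estimate. Significance tests at these sample sizes miss a 0.5 SD imbalance about half the time between the integrated units and about three times in ten between models, so they cannot certify comparability.

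The bias could reach 0.15–0.25 SD at a pre-post correlation of 0.5, and 0.09–0.35 SD over correlations of 0.3–0.7. This depends on an assumed imbalance of 0.3–0.5 SD and on regression to a common mean. It shows what the plan is exposed to, not that such an imbalance will occur. Adjustment deals only with measured consumer case-mix; confounding by site and district remains whatever model is used.

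**What to change.** 1. Pre-specify as the primary estimate a linear model of follow-up HoNOS on staffing model, baseline-window HoNOS, age, sex, diagnosis, prior-year inpatient bed days and baseline LSP-16. Leave out site and all post-admission variables, and fix the covariates without selection by p-value. Report the staffing coefficient with its confidence interval and base the equivalence conclusion on it.
2. Keep the unadjusted change-score comparison as a sensitivity analysis. State what separates the two: the model assumes that, without a staffing effect, consumers with equal baseline values would have equal expected follow-up in both groups; the change score assumes equal average change.
3. Combine Bayside and Logan regardless of baseline p-values. Describe imbalance with standardised differences, and show each integrated unit against Coorparoo alongside.
4. State that adjustment removes only measured case-mix differences and that, with one clinical unit, staffing model cannot be separated from site or district.

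The cost is wording and a few degrees of freedom; every covariate is already planned for collection. In balanced groups, adjusting for baseline HoNOS leaves (1 − ρ²)/(2(1 − ρ)) = (1 + ρ)/2 of the change-score variance, or 65–85% for ρ of 0.3–0.7, so precision should improve. LSP-16 is routinely collected only in community residential and ambulatory services (Table 2 footnote). Some baseline values will therefore be missing and will fall to the multiple imputation already planned.

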**Discussion:**

It is expected that the new knowledge gained through this study will guide the adaptation of these and similar services. For example, if differential outcomes are achieved for consumers under the integrated and clinical staffing models this may inform staffing guidelines.

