### Sample

The project is currently in progress. The cohort will comprise all consumers admitted to the three MSAMHS CCUs (Bayside, Coorparoo and Logan) between December 2014 and December 2017 who provide informed consent to participate. Baseline and follow-up data will be sourced from administrative datasets for the 12-month period prior to and following CCU admission and discharge respectively.

As the study takes a naturalistic observational design, the only defined inclusion criteria is acceptance for a trial of CCU based rehabilitation care. Each CCU provides a six-week assessment period to establish suitability for engagement under the model of service. Given this, consumers who are discharged prior to the conclusion of this assessment period will be excluded from the study. This exclusion criterion assists in ensuring that included participants are aligned with the model of service. This reflects a modified intention-to-treat approach [34], as participants will be included regardless of their mode of exit from the CCU (planned/unplanned (CCU initiated)/unplanned (consumer initiated).

Based on anticipated service throughput, with a median length of stay at the Coorparoo CCU of 0.9 years (inter-quartile range 0.50-1.8 years) at a point estimate in 2013, and assuming a 70 % response rate, it was expected that at least 60 consumers from the integrated staffing model and 40 from the clinical staffing model would agree to participate over the study period. This minimum sample likely reflects an under-estimate given 37 unique admissions occurred to the Coorparoo CCU in the 12-month period from July 2012. Additionally, since the opening of the Bayside and Logan CCUs 50 of the 63 consumers admitted across all three sites met the inclusion criteria (79.4 %) and 42 (84.0 %) of eligible consumers provided consent to participate.

The adequacy of the estimated minimum sample size was considered using the Epi Info™ StatCalc program [35] for unmatched or cross-sectional cohort studies. This minimum sample was estimated to provide greater than 80 % power to detect a 15 % difference in outcome on the primary outcome measure at the 95 % confidence interval using the Fleiss calculation. The acceptability of this power is supported by an emergent difference of 20 % in outcome HoNOS scores in a recent Australian study examining outcomes of a community residential service for similar consumers [36].

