Multiple sources of potential bias need to be considered in the qualitative analysis. Retrospective biases are likely to impact comparison recall of alternative care and work settings for both consumers and staff [81]. There are specific challenges associated with the consumer sample. The risk of deficits and bias in the self-report of persons with schizophrenia, especially around functional capacity, are well documented [82]. There is also a risk that the provision of a gratuity to consumers creates an undue incentive to participate [83], and that a self-selected and financially incentivized consumer group do not adequately reflect the general population of service users [84]. The inherent power differential associated with the consumer role within the service under investigation creates a risk of pseudo-participation [29]. Additionally, for staff participants the dual roles of several members of the research team may inhibit more negative disclosures about their work experiences. Given these issues, careful and ongoing attention to the collaborative involvement of participants and the creation of a safe space for participation is needed.

There is very limited research exploring the outcomes and experience of community based residential mental health rehabilitation care. The generalisability of results from the present study will be limited by the focus on a single model of service and two sites for the integrated staffing and a single site for the traditional clinical staffing model. It is possible that idiosyncratic aspects of practice at each site or under the two staffing models will impact on the outcomes of the study. However, the richness of detail facilitated by taking a longitudinal mixed methods approach incorporating multiple stakeholder perspectives is anticipated to facilitate relevant inferences to guide practice in alternative contexts.

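### Staffing model is fixed by site (one clinical unit, two integrated units), but the primary test and the power check leave out between-site variation, so the standard error is too small for a conclusion about staffing models.

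*Protocol article*

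**What the plan says.** **Exposure.** Evaluation context and Table 1 give Coorparoo a clinical staffing model, and Bayside and Logan an integrated one. The closing Discussion counts "two sites for the integrated staffing and a single site for the traditional clinical staffing model".

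**Primary test.** Under Quantitative methodology, Analysis: "differences in the total HoNOS score pre admission and post discharge will be assessed using a t-test or Mann–Whitney U test", depending on normality, with "statistical significance will be assessed at a level of 0.05". The same section says that, if the cohorts are comparable, "it is planned that the data from the two integrated staffing model sites will be able to be combined". No site term is attached to this test.

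**Sample size.** The Sample section expects "at least 60 consumers from the integrated staffing model and 40 from the clinical staffing model". It checks this with an Epi Info routine "for unmatched or cross-sectional cohort studies" and reports "greater than 80 % power to detect a 15 % difference in outcome". No allowance for clustering is mentioned.

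**Intended use.** The abstract's Discussion says that "if differential outcomes are achieved for consumers under the integrated and clinical staffing models this may inform staffing guidelines".

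**Where site does appear.** Table 4 lists CCU site as a three-category predictor in the hierarchical regression, entered after staffing model. The Discussion acknowledges non-random allocation and says that practice peculiar to a site may affect outcomes.

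**The concern.** The question concerns staffing models, and the study has three units carrying that exposure, not 100. A t-test or Mann–Whitney test on pooled consumers measures the difference against consumer-to-consumer variation alone. Any ordinary difference between units in HoNOS change then goes into the staffing contrast without entering its error term.

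The document itself gives reason to expect such differences. Table 1 shows disadvantage percentile ranks of 90, 83 and 46, and different local availability of inpatient rehabilitation beds, transitional housing, community rehabilitation and homelessness teams. Evaluation context names location, alongside staffing, as what distinguishes the sites. The Discussion expects referral patterns to differ by site.

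The comparability check before pooling looks at the cohorts' characteristics. Similar cohorts can still change differently at Bayside and Logan.

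At stake is the strength of evidence claimed for a staffing policy. Site variation could produce an apparent staffing difference, or offset a real one so that the models look alike.

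**Working it through.** **1. The plan's own figure.** The stated power is above 80% for a 15% difference with 60 v 40. Neither a base proportion nor an SD is given. Taking 15% as percentage points in a two-sided two-proportion calculation without clustering, power is about 31% to 44% for clinical-group proportions of 0.3 to 0.7. It passes 80% only when the integrated-group proportion is about 0.5% or less, or 99.5% or more. Taken as a difference in means, 80% power needs about 0.57 SD. The stated figure was therefore not reproduced. That is a separate matter, and nothing below depends on it.

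**2. Inputs.**
- nC = 40 and nI = 60 (Sample).
- One clinical and two integrated sites (Table 1, Discussion).
- Significance level 0.05 (Analysis); two-sided is assumed, since sidedness is not stated.
- Total SD of HoNOS change set to 1.
- ICC: not given in the documents; assumed range 0.01 to 0.10.
- Integrated sites taken as about equal in size.

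**3. Formulas.**
- Variance assumed by the planned test: 1/nC + 1/nI = 1/40 + 1/60 = 0.0417, so SE = 0.204.
- Variance allowing for site: (1 − ICC)(1/nC + 1/nI) + ICC(1 + 1/2). The second term is one site effect on the clinical side plus the mean of two on the integrated side.
- False-positive rate of the planned test with no staffing effect: 2[1 − Φ(1.96 / SE ratio)].
- Effective sample size: 100 / variance ratio.

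**4. Example at ICC 0.05.** 0.95 × 0.0417 + 0.05 × 1.5 = 0.0396 + 0.0750 = 0.1146. The variance ratio is 0.1146/0.0417 = 2.75 and the SE ratio is 1.66. The false-positive rate is 2[1 − Φ(1.96/1.66)], about 24%. The effective sample size is 100/2.75, about 36.

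**5. Over the assumed range.**

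| ICC | True variance | SE ratio | False positives, formula | False positives, simulated t-test | Effective N |
|---|---|---|---|---|---|
| 0 | 0.0417 | 1.00 | 5% | 5.1% | 100 |
| 0.01 | 0.0563 | 1.16 | 9.2% | 9.1% | 74 |
| 0.05 | 0.1146 | 1.66 | 23.7% | 24.4% | 36 |
| 0.10 | 0.1875 | 2.12 | 35.6% | 37.0% | 22 |

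The simulation used 40,000 trials per ICC, with sites of 40, 33 and 27. With that uneven integrated split the SE ratio is still 1.16 at ICC 0.01 and 1.66 at 0.05, so the equal-size assumption matters little.

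**6. More consumers do not remove it.** The term 1.5 × ICC does not contain n. At ICC 0.05 it is 0.075, so chance site differences alone give the contrast a standard deviation of √0.075 = 0.27 SD however many consumers are recruited (0.12 SD at ICC 0.01, 0.39 SD at 0.10). A shift of that size can fall in either direction, which is how it can mimic or mask a staffing difference.

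**The case against.** **The protocol is open about this.** It is. The Discussion says that lack of randomisation hinders causal inference and that site practice may affect outcomes. A reader might infer that the plan ignores site differences; the text does not support that. But the caveats leave the test and the power check unchanged.

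**Site is in the regression.** True, and useful: once staffing model is entered, CCU site adds exactly the Bayside v Logan contrast on the same outcome. It does not repair the primary comparison. Staffing model is an exact function of site, site enters as an ordinary predictor, and the regression is a secondary exploration of predictors.

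**The ICC may be small.** This stands. The outcome is a within-person change, measured before entry and after discharge. The Discussion describes the primary-outcome assessors as independent of the units, HoNOS scoring is calibrated across sites, and the units share a model of service and governance. None of this shows an ICC of zero, but it leaves any single central value unsupported.

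**False positives are the wrong error for an equivalence aim.** Partly right. A spurious difference works against the expected result. The opposite error, a real difference masked by site effects, has the same source. It cannot be quantified from the documents without an equivalence margin.

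**The Analysis section names a test, not an interval.** Correct. A remark about narrow intervals applies only to the interval that the t-test implies.

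**It is a design limit.** Largely so. With one clinical site no analysis can estimate that site's variance. What can change is the claim made and how its uncertainty is shown.

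**Conclusion.** The point holds in this form: the primary test and the power check treat between-site variation as zero, so for any ICC above 0 the standard error is too small for a conclusion about staffing models. With 40 v 60 consumers it is understated 1.16-fold at ICC 0.01, 1.66-fold at 0.05 and 2.12-fold at 0.10. These sizes rest on assumed ICCs, a two-sided 5% test and about equal integrated sites; only the direction is independent of the ICC chosen.

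Two stronger readings are not supported. One is that the study has a false-positive rate of about 24%: that follows only if the ICC is 0.05, and at 0.01 it is about 9%. The other is that the test is invalid for any purpose: as a comparison of these three particular units, its ordinary standard error does not have this defect. The defect arises when the result is carried over to staffing models in general, as the abstract intends.

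**What to change.** **(a) Analysis: report by site.** Give HoNOS change with an interval for each of the three sites. Always report the Bayside–Logan difference in change beside the primary contrast. Do not use it as a significance gate for pooling; with about 30 consumers per site it would be a weak pretest.

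**(b) Analysis: name the contrast for what it is.** Call it Coorparoo v Bayside/Logan and state that its ordinary interval applies to these three units only. This changes the inference claimed, not the standard error: with 30 + 30 integrated consumers, Coorparoo v the mean of the two sites has variance 1/40 + ¼(1/30 + 1/30) = 1/40 + 1/60, the same as the planned test.

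**(c) Analysis: add a prespecified sensitivity interval.** Use variance σ²[(1 − ICC)(1/nC + 1/nI) + ICC(1 + 1/2)], for about equal integrated sites, over a stated range such as 0.01 to 0.10. Report how the conclusion changes across the range, and limit attribution to staffing model accordingly. Do not make it a pass/fail rule: at ICC 0.10 the 95% half-width is 1.96 × √0.1875, about 0.85 SD, so requiring a result to survive the whole range would largely settle the answer in advance.

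**(d) Sample.** State that the power figure assumes no between-site variation, and give the effective sample size over the same range (about 74 to 22 for the planned 100).

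**Cost.** Wording and a short calculation, which can be settled while the study is still in progress. No extra consumers or sites are needed. The price is a wider interval and a more cautious claim about staffing model.
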